**5.4.2 Laboratory Samples**

Approximately 4 tablespoons of venous blood will be collected by either a certified phlebotomist or registered nurse for the following cardiovascular, metabolic and inflammatory markers including but not limited to:

*Cardiovascular and Metabolic biomarkers**

Lipid panel (such as cholesterol, HDL, LDL)

NMR lipid analysis

Apolipoprotein panel (Apo A-1, Apo B, Apo B/Apo A-1)

Fasting blood glucose

Fasting insulin

*Stress markers*

Cortisol: Serum

*Inflammatory Markers*

TNF-α**

IL-6**

hs-CRP

**Note:** *=Participants will need to be fasting for 10 – 12 hours pre-specimen collection; **=Research lab samples will be processed by [name] lab.

***Instructions for blood sampling:***

Study participants will be instructed verbally and given the following written instructions to prepare for blood sampling. Please report to the outpatient phlebotomy area for blood work in the morning. Please do not eat for 10 – 12 hours before blood work collection.

**5.4.3 Laboratory Sample Routing**

The following samples will be sent for processing in the **Clinical Center Department of Laboratory Medicine:**

Lipid panel, NMR analysis**,** Apolipoprotein panel (Apo A-1, Apo B, Apo B/Apo A-1), serum cortisol, hs-CRP.

The following laboratory samples will be sent for processing to **[name] research lab, [name]:**

TNF-α, IL-6.

##

## 5.5 Telephone Script and Exit Interview-Appendix J

The Intervention Group will participate in a brief telephone follow-up at weeks two and four, as well an exit interview at week six. The control group will participate in an exit interview at week six. The length of the interview is projected to be from 10 - 15 minutes.

## 5.6 Implementation Log- Appendix E

A study implementation log will be used to track subject participation in UCE and the details of the initial 1:1 intervention session.

# 6.0 BIOSTATISTICAL CONSIDERATIONS

## 6.1 Sample size

The study is a randomized controlled trial with two groups: stress reduction and control (standard education) using permuted block randomization with allocation ratio of 1:1. The primary objective of this study is to investigate whether HSCT caregivers in the stress reduction group demonstrate improved levels of stress compared to those in the control group. Power analysis was performed based on the primary objective only. We used a two-sided hypothesis that the PSS level will differ between the intervention group and the control group. We assume an exchangeable correlation structure of PSS. Based on an effect size of 0.6 [^40^](#_ENREF_40)^,^[^85^](#_ENREF_85) and correlation of 0.80 between two time points from our biomarker study, with 80% power and type I error of 0.05, in order to detect a difference between the stress reduction group and the control group, we will need 39 participants in each group and a total sample size of 78 [^86^](#_ENREF_86).

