**Appendices**

Appendix A: Sequence for Yoga Practice File

Appendix B: Treatment Fidelity

Appendix C: Demographic Interview

Appendix D: Telephone Script and Exit Interview

Appendix E: Subject Practice Log

# STUDY OBJECTIVES & RESEARCH HYPOTHESES

## **Study Objectives & Hypotheses**

## Primary Objectives & Hypotheses

- - - 1. To examine whether HSCT caregivers participating in a stress reduction intervention demonstrate improved levels of perceived stress compared to HSCT caregivers in the control group.
         1. ***Hypothesis:*** The level of perceived stress will differ between HSCT caregivers in the control group and HSCT caregivers who participate in a stress reduction intervention.

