## 6.2 Statistical Analyses

Initial data analysis will consist of examining the frequency distributions for all variables at both time points and computing descriptive statistics appropriate for the level of measurement (e.g., mean and standard deviation for interval level data, median for ordinal level data). Linear mixed repeated measures analysis will be used to analyze the effect of intervention on the primary outcome of perceived stress. The primary analysis will be based on intention-to-treat, which will include all of the randomized subjects. The last observation carried forward method will be used to impute missing data. However, if an enrolled subject comes off study before being randomized, they will be replaced. A sensitivity analysis will be performed for all subjects with complete data at both time points.

The effect of intervention on the exploratory outcome variables as described in the objective section will also be examined by linear mixed models. Any demographic covariates will be included in the model if significantly associated with the outcome and significantly different between the groups. To examine the effect of practice variation on the study outcomes, practice time will be included in the linear mixed models for the intervention group only. Aikake information criterion and the Bayesian information criterion will be used to select best fitting models. Appropriate data transformation technique will be used if necessary.

If no significant differences are found between groups, the responders with clinically meaningful changes in the intervention group will then be characterized. No minimal clinically important differences have been established for our primary outcome, the PSS, therefore, we will use the method proposed by Norman, Sloan, and Wyrwich (2003) of accepting changes in .5 standard deviation as clinically important [^87^](#_ENREF_87). Responders and non-responders will be compared on the basis of their demographic characteristics such as gender and age.

In addition to the primary analysis outlined above, exploratory hypotheses generating analyses will be performed to examine the relationships among caregiver factors. Methods of correlation and regression analysis will be used to evaluate the relationships between outcomes of interest and study variables. All inferential tests will be conducted at the .05 level of significance.

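### The 39 per group in Section 6.1 matches a group difference averaged over baseline and week 6, so the stated 80% power does not belong to any standard test of the intervention

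*Protocol*

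**What the plan says.** Section 6.1 bases the power analysis on the primary objective alone. The test is two-sided: "We used a two-sided hypothesis that the PSS level will differ between the intervention group and the control group". The other inputs are an exchangeable correlation structure, "Based on an effect size of 0.6", and a "correlation of 0.80 between two time points from our biomarker study, with 80% power and type I error of 0.05". The result is that "we will need 39 participants in each group and a total sample size of 78". A textbook on longitudinal analysis is cited, but no formula, variance factor or contrast is given, and the 0.6 is not said to be in SD of the score or SD of the change.

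Perceived stress is measured twice, at baseline and at week 6 (Section 3.0 and Figure 3). Section 3.2 places the baseline measures before the intervention session.

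The primary hypothesis reads: "The level of perceived stress will differ between HSCT caregivers in the control group and HSCT caregivers who participate in a stress reduction intervention". Section 6.2 says: "Linear mixed repeated measures analysis will be used to analyze the effect of intervention on the primary outcome of perceived stress". It does not say which model term carries that effect.

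**The concern.** In a randomised trial with one pre-treatment and one post-treatment measurement, the arms are expected to be equal at baseline and to differ only at week 6. A sample size that uses the correlation between the visits should therefore rest on the change, the group-by-time term, or the week-6 difference adjusted for baseline. For all of these, a higher correlation reduces the number needed.

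The 39 in Section 6.1 behaves the other way. It matches the variance of the average of the two visits, where a higher correlation raises the number needed. That calculation is sound when both measurements follow treatment and the effect is present at both. Here it counts the pre-treatment score as if it already carried the full 0.6 SD.

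Two things are at stake. The stated 80% does not describe the trial, so readers cannot tell from it what effect the trial can detect. Also, an analyst who took the powered contrast as the primary test would dilute a real week-6 effect by half.

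**Working it through.** **Inputs.** From Section 6.1: two-sided alpha 0.05 (z = 1.960), power 80% (z = 0.842), effect d = 0.6, exchangeable correlation ρ = 0.80, 1:1 allocation, 39 per group. From Sections 3.0 and 3.2: two measurements, the first before the intervention.

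**Formula.** With the score variance set to 1 and V the variance of the contrast analysed, n per arm = 2(1.960 + 0.842)² × V / 0.6² = 43.60 × V.

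**Reproducing the plan's figure.**

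| Contrast | V at ρ = 0.80 | 43.60 × V | Rounded up |
|---|---|---|---|
| Mean of the two visits | (1 + ρ)/2 = 0.90 | 39.24 | 40 |
| Week 6 only | 1 | 43.60 | 44 |
| Change, or group-by-time | 2(1 − ρ) = 0.40 | 17.44 | 18 |
| Week 6 adjusted for baseline | 1 − ρ² = 0.36 | 15.70 | 16 |

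Only the first row lands on 39 (to the nearest integer; normal-approximation power at 39 is 79.8%). To reach 39 from the change contrast, ρ would have to be about 0.55; from the baseline-adjusted contrast, about 0.32. One other route to 39 was found: a one-sided week-6-only test needs 35, which becomes 39 after inflation for 10% dropout. It contradicts the stated two-sided test and makes no use of the correlation.

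**What the averaged contrast gives in this design.** With no expected difference at baseline and 0.6 SD at week 6, the averaged difference is (0 + 0.6)/2 = 0.3 SD. The number needed for 80% power becomes 2 × 7.849 × 0.90 / 0.09 ≈ 157 per arm.

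**Power at 39 per arm, week-6 effect 0.6 score-SD** (noncentral t, 76 degrees of freedom):

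| Test | ρ = 0.80 | ρ = 0.50 |
|---|---|---|
| Group main effect over both visits | 28% | 33% |
| Week 6 only | 74% | 74% |
| Change, or group-by-time | 98.5% | 74% |
| Week 6 adjusted for baseline | 99% | 86% |

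A simulation of 20,000 trials at ρ = 0.80 agrees: 27.9% for the averaged test, 74.1% for week 6 only, 98.6% for change. When the 0.6 difference is placed at both visits, the averaged test has 79.1% and the change test 4.9%. So the stated power is recovered only where the intervention has changed nothing between the visits. With no difference at either visit, the averaged test rejects in 5.0% of trials.

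**If 0.6 is in SD-of-change units.** The change test then has a standardised effect of 0.6 with V = 1, so it needs 44 per arm and has about 74% power at 39.

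**Detectable effect.** For the baseline-adjusted test at 80% power, d = 2.802 × √(2(1 − ρ²)/39). This is 0.38 SD at ρ = 0.80 and 0.55 SD at ρ = 0.50 (normal approximation).

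**The case against.** The protocol never states the formula. It is inferred from the arithmetic, and the match is to 39.24, which strict rounding takes to 40. The effect size is printed to one decimal: an unrounded 0.635 to 0.64 would give 38.9 to 38.3 per arm, hence 39, from an ordinary two-group comparison at week 6. This stands as a caution. But that route leaves the correlation and the exchangeable structure without any role, although Section 6.1 presents both as inputs.

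Three stronger readings are tempting, and the documents do not support them.

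- A reader might infer that the primary test is invalid. It is not: under randomisation the averaged group comparison keeps its 5% type I error. The fault is in the power claim.
- A reader might infer that the protocol commits to the group main effect, so that the trial really has 28% power. The hypothesis does speak of the level differing between groups, but the objective speaks of improvement, and Section 6.2 defines responders by change. Section 6.2 names no term, and a statistical analysis plan that is not shown may name one. That silence is not the finding; the power figure stated in Section 6.1 is.
- A reader might infer that 78 is too few, or conversely that power is certainly 98% to 99%. Neither follows. The answer depends on the contrast, on the scale of the 0.6 and on the correlation.

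**Conclusion.** With the inputs as printed, the 39 per group is consistent only with a group difference averaged over baseline and week 6. Because baseline precedes the intervention, the 80% is not the power of any standard test of the intervention. Depending on the contrast, the power at 39 per arm with a 0.6 score-SD effect at week 6 and ρ = 0.80 runs from about 28% to about 99%.

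This rests on four assumptions: 0.6 is taken as exact; it is in SD of the score unless stated otherwise; the variances are equal at the two visits; and there are no missing data. The figures are before the 10% attrition reported from the earlier caregiver study in Section 10.1. For a change or baseline-adjusted test with 0.6 in score-SD units and ρ = 0.80, N = 78 is ample. For week 6 alone, or for the change test if 0.6 is in SD-of-change units, power is about 74%, short of 80%.

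**What to change.** In Section 6.2, name the primary test as the between-arm difference in week-6 perceived stress adjusted for baseline, by ANCOVA or by a mixed model with the baseline means constrained to be equal. State that the group main effect averaged over the visits is not the test. An unconstrained group-by-time term is not the same thing: its variance factor is 0.40 against 0.36 at ρ = 0.80, and its power is 74% against 86% at ρ = 0.50.

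In Section 6.1, state whether the 0.6 is in SD of the score or SD of the change, and replace the calculation with the one for the named contrast. Restate power at N = 78 over correlations of 0.5 to 0.8: about 86% to 99% for a 0.6 score-SD effect or, equivalently, 80% power for about 0.55 down to 0.38 SD. Say that these figures are before the 10% attrition given in Section 10.1.

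The cost is an amendment to the wording of two sections, with no change in N, visits or data collected.

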## 6.2 Statistical Analyses

Initial data analysis will consist of examining the frequency distributions for all variables at both time points and computing descriptive statistics appropriate for the level of measurement (e.g., mean and standard deviation for interval level data, median for ordinal level data). Linear mixed repeated measures analysis will be used to analyze the effect of intervention on the primary outcome of perceived stress. The primary analysis will be based on intention-to-treat, which will include all of the randomized subjects. The last observation carried forward method will be used to impute missing data. However, if an enrolled subject comes off study before being randomized, they will be replaced. A sensitivity analysis will be performed for all subjects with complete data at both time points.

The effect of intervention on the exploratory outcome variables as described in the objective section will also be examined by linear mixed models. Any demographic covariates will be included in the model if significantly associated with the outcome and significantly different between the groups. To examine the effect of practice variation on the study outcomes, practice time will be included in the linear mixed models for the intervention group only. Aikake information criterion and the Bayesian information criterion will be used to select best fitting models. Appropriate data transformation technique will be used if necessary.

If no significant differences are found between groups, the responders with clinically meaningful changes in the intervention group will then be characterized. No minimal clinically important differences have been established for our primary outcome, the PSS, therefore, we will use the method proposed by Norman, Sloan, and Wyrwich (2003) of accepting changes in .5 standard deviation as clinically important [^87^](#_ENREF_87). Responders and non-responders will be compared on the basis of their demographic characteristics such as gender and age.

In addition to the primary analysis outlined above, exploratory hypotheses generating analyses will be performed to examine the relationships among caregiver factors. Methods of correlation and regression analysis will be used to evaluate the relationships between outcomes of interest and study variables. All inferential tests will be conducted at the .05 level of significance.

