All participants will receive usual care education (UCE), which includes transplant specific information for the recipient and the caregiver, as well as caregiver resources. After study enrollment, caregiver subjects will be randomized to either the control group or the intervention group. A permuted block randomization with allocation ratio of 1:1 will be performed by the study statistician. All participants will meet 1:1 with a study investigator to review the UCE materials. Participants in the intervention group will also receive an audio recording of a 20 minute yoga-based stress reduction intervention, as well as instructions on how to complete the intervention; they will be asked to practice the twenty minute audio file daily for the six weeks of the intervention. The six-week length of the intervention, as well as the 20 minute time of the audio file, was selected based upon the length of similar interventions in other caregiver populations, with interventions ranging between four to ten weeks [^37^](#_ENREF_37)^,^[^43^](#_ENREF_43). All study visits will be scheduled around the HSCT recipient’s schedule and visits to minimize burden for the caregiver. The initial visit for all participants will occur prior to the patient’s initial discharge from the hospital and within 7 days of the HSCT infusion (Day 0+7). Subjects in the intervention group will receive a brief phone call at weeks two and four (+/- 7 days) to assess progress and to record practice. All subjects will participate in an exit interview at week six (+/- 7 days). Study questionnaires will be administered to all subjects at baseline and again at week six (+/- 7 days). Completion will take approximately 20 minutes through a web-based system. If the electronic system is unavailable, a hard copy of the questionnaires will be available for completion. Caregivers in either group who complete baseline assessments but are no longer able to return to the clinical center for their week 6 study visit will be given the option to complete the week 6 questionnaires electronically.

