## 3.2 Experimental Intervention – Stress reduction intervention Appendix A

After baseline measures have been obtained and subjects have been randomized into the intervention and control groups, subjects in the intervention group will meet with the interventionist for approximately 20 minutes to go over instructions for performing the gentle chair yoga and breath work that they will be asked to perform daily using a 20-minute audio recording that they will receive in this meeting. The stress reduction intervention (Appendix A) will be provided to subjects by a trained interventionist. The intervention will be delivered by [name], RN, who is a registered nurse with a master’s degree in psychiatric-mental health nursing, and is a certified Iyengar Yoga Instructor, or by study staff who have received training by [name]. Participants will then practice the recording one time under the supervision of study staff.

The audio recording was developed by Advanced Iyengar Yoga Instructor, [name], who has over 35 years of experience teaching yoga and has recorded numerous audiotapes of yoga for home practice. [name] worked with [name] to develop the intervention, based upon [name] years of teaching experience, as well as the research literature that shows the effectiveness of similar yogic breathing exercises in reducing levels of perceived stress [^53^](#_ENREF_53) and similar chair-based yoga interventions in improving levels of depression, anxiety, quality of life, and well-being in elderly populations [^54^](#_ENREF_54)^,^[^55^](#_ENREF_55). The 20-minute audio recording will lead participants through a series of gentle stretching and breathing exercises [^53-55^](#_ENREF_53). The first few poses will be performed standing, using the wall for support. The remainder of the audio file will consist of gentle seated yoga poses (stretches and twists) that are performed in a chair, as well as guided breathing exercises that focus primarily on slowing and quieting the inhalations and exhalations.

Small (<5 GB) audio players will be purchased and given to subjects in the intervention group. These devices will be preloaded with the 20-minute audio file of the stress reduction intervention. Upon completion of the study, control group subjects will also receive an audio player with the intervention recording and no subjects will be asked to return their device.

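### Section 6.2 leaves the baseline value and the tested contrast open in the primary perceived-stress model; a baseline-adjusted week-6 difference would be at least as precise and would remove the ambiguity

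*Protocol*

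**What the plan says.** Protocol section 6.2 gives the primary analysis in one sentence: "Linear mixed repeated measures analysis will be used to analyze the effect of intervention on the primary outcome of perceived stress". Section 3.0 sets the measurement times: "Study questionnaires will be administered to all subjects at baseline and again at week six (+/- 7 days". Figure 3 agrees, so there is one post-baseline value per caregiver.

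The only covariate rule, placed in the paragraph on exploratory outcomes, reads: "Any demographic covariates will be included in the model if significantly associated with the outcome and significantly different between the groups". It covers demographic variables. Baseline perceived stress is not named as a covariate anywhere.

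Section 6.1 sizes the trial on the primary objective. It says "We used a two-sided hypothesis that the PSS level will differ between the intervention group and the control group" and "We assume an exchangeable correlation structure of PSS". Its inputs are "Based on an effect size of 0.6" and a "correlation of 0.80 between two time points from our biomarker study", with 80% power and type I error 0.05, giving 39 per group and 78 in total.

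Section 3.2 describes the first intervention session as coming "After baseline measures have been obtained and subjects have been randomized into the intervention and control groups".

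**The concern.** With two visits, a repeated-measures model of perceived stress must carry baseline in the response vector. That does no harm if the model gives both arms one baseline mean. If the baseline means are left free, the result depends on which contrast is tested, and the two usual ones behave differently:

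- **Group-by-time** subtracts the whole baseline difference. This is valid, but less precise than adjustment, and it slightly over-corrects a chance imbalance.
- **Group main effect over both visits** averages a baseline difference that cannot reflect treatment with a week-6 difference that can. This dilutes the effect and passes most of any baseline imbalance into the estimate.

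Section 6.2 does not choose between them, and the hypothesis in 6.1 about the level of stress does not settle it. In a trial of 78, the choice affects the width of the confidence interval. Under the second contrast, it also affects whether the trial can find the effect it was planned for.

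**Working it through.** **Inputs from the protocol.** Effect d = 0.6 SD, correlation ρ = 0.80, two-sided α = 0.05, power 80%, n = 39 per arm (section 6.1); two visits (section 3.0). The formulas assume complete data, equal variances at the two visits and no treatment effect at baseline.

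**Reproducing the stated sample size.** Per arm, n = 2(1.960 + 0.842)² V / d² = 43.6 V, where V is the variance of the per-caregiver quantity compared, in SD² units.

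| Contrast | V | V at ρ = 0.80 | n per arm |
|---|---|---|---|
| Week 6 only | 1 | 1.00 | 43.6 → 44 |
| Mean of both visits | (1+ρ)/2 | 0.90 | 39.2 |
| Change score (unconstrained group-by-time) | 2(1−ρ) | 0.40 | 17.4 → 18 |
| Baseline-adjusted | 1−ρ² | 0.36 | 15.7 → 16 |

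Only the mean of both visits gives 39 (39.2, rounded to nearest; power at 39 is 79.8%). That calculation counts baseline as a second outcome carrying the full 0.6 effect.

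**Precision at 39 per arm.** SE = √(2V/39).

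- Change score: √(0.80/39) = 0.143 SD; power for 0.6 SD is 98.7%.
- Baseline-adjusted: √(0.72/39) = 0.136 SD; power 99.3%.
- Variance ratio, adjusted to change: (1−ρ²)/[2(1−ρ)] = (1+ρ)/2 = 0.90. The gain is the same as 78/0.90 ≈ 87 caregivers.
- If ρ were 0.50 (an assumption, not a protocol figure): SE 0.227 against 0.196 SD, ratio 0.75, power 75% against 86%.

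**Effect of a chance baseline imbalance.** One standard error of the baseline difference is √(2/39) = 0.226 SD. Given a baseline difference b, the expected week-6 difference is d + ρb.

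- Change score: d − (1−ρ)b. The slope is −0.20, so a one-SE imbalance moves the estimate by 0.20 × 0.226 = 0.045 SD, opposite in direction to the imbalance.
- Mean of both visits: d/2 + [(1+ρ)/2]b. The slope is +0.90, so the shift is 0.90 × 0.226 = 0.20 SD, in the direction of the imbalance.
- Baseline-adjusted: slope 0.

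A simulation of arm-mean differences at 39 per arm gave slopes of −0.201, +0.900 and −0.001.

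**Power if the mean of both visits is tested.** The baseline difference is zero on average, so the expected contrast is (0 + 0.6)/2 = 0.3 SD. With SE √(1.80/39) = 0.215 SD, power is about 29%. Reaching 80% would need 43.6 × 0.90 × (0.6/0.3)² ≈ 157 per arm.

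**The case against.** The strongest reply is that section 6.2 does not contain the fault. It never says that the baseline means are free. A mixed model with a common baseline mean is itself a repeated-measures mixed model with baseline as a response, so the sentence fits the remedy as well as the problem. Mean structure, covariance and contrast are often left to a statistical analysis plan, which is not at hand. This stands as far as it goes: a reader might infer that the protocol commits to an inefficient estimator, and its text does not say so.

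The size is also open to challenge. At ρ = 0.80 the group-by-time contrast has a standard error only about 5% larger, and power above 98% either way. The larger gains need lower correlations that the protocol does not give. This stands too.

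A reader might further infer that the treatment effect would be biased. It would not: each contrast is unbiased over randomisation for what it estimates, and the shifts above are conditional on the observed imbalance. Nor do the documents show that the trial has 29% power. That figure applies only if the two-visit average is tested, and the link to it is the arithmetic of 6.1, not a statement in 6.2.

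Lastly, section 3.2 lists baseline before randomisation without expressly ordering the two, and Figure 3 puts both in one window. Baseline still precedes the first intervention session, which is what the argument needs most.

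The reply does not remove the open choice. The one figure that the protocol does fix, 39 per arm, matches the least suitable contrast.

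**Conclusion.** The point holds as a low-cost improvement. It does not show that the planned analysis is invalid. As written, section 6.2 neither adjusts for baseline perceived stress, nor equates the baseline means, nor names the contrast.

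If group-by-time is intended, the cost is modest: adjustment would cut the variance by 10% at the protocol's correlation. If the two-visit average is intended, the cost is serious: half the expected effect, about 90% of any baseline imbalance and about 29% power. The documents do not establish which is meant.

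These sizes rest on 39 complete pairs per arm, equal variances and ρ = 0.80. Section 6.2 fills missing values by carrying the last observation forward, and section 10.1 reports 10% attrition in an earlier caregiver study, so the realised figures will differ somewhat.

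**What to change.** In section 6.2, state that the primary estimate is the between-group difference in perceived stress at week 6, obtained in one of two ways:

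- a mixed model with both visits as responses, one baseline mean common to both arms and an unstructured covariance; or
- ANCOVA of week-6 perceived stress on arm and baseline perceived stress.

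The two are close to equivalent with complete data. Without imputation, ANCOVA drops caregivers who lack a week-6 value and the mixed model keeps them. Use the same form for exploratory outcomes measured at both visits.

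The cost is one sentence. Baseline is already collected, no visit or assay is added, and in large samples the variance is never higher than with the change score. The sample size text in 6.1 should then name the same contrast. On its own inputs, 39 per arm is ample for it (16 per arm needed before attrition), so the change does not raise the target.
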